### Laboratory Procedures

#### Gut Colonization

Rectal swabs and stool samples will be tested for the presence of the probiotic species and strains used in this study using quantitative polymerase chain reaction (qPCR). Assays will be performed at the PNGIMR using an in-house method developed and optimized for local laboratory conditions. Briefly, total DNA will be extracted from approximately 200 mg of stool or 600 to 800 µL of rectal swab eNat preservation medium using the FastDNA Spin Kit for Soil (MP Biomedicals), incorporating a bead*-*beating step to enhance bacterial cell wall disruption.

Singleplex qPCR reactions will be used to detect *B longum* subspecies *infantis* and *L plantarum*, using the TaqMan Fast Advanced Master Mix (Thermo Fisher Scientific). Standard curves will be generated from DNA extracted from quantified cultures of *B longum* subspecies *infantis* and *L plantarum* grown either at the PNGIMR or at Federation University, Australia.

The primer and probe sequences to be used for *B longum* subspecies *infantis* are as follows:

Bi26_Forward 5 - GTCACGATGTCTCCTTTGATATCA GCATG-3′Bi26_Reverse 5′- CCTTTTGCGTCTCCCCCG-3′Bi26_Probe 5 - FAM-TCATTCATTGTAGTGGCGATCAC CGTTACC-3′

The primer and probe sequences to be used for *L plantarum* are as follows:

Lp_Forward 5′-ACAAATGGCAGGGCGAAAAATG-3′Lp_Reverse 5′-TTCTACATCCGGGCAAACCTTG-3′Lp_Probe 5′- FAM-ACGGAGCTTCTATGACGATGCTT TCA-3′

#### Pneumococcal Carriage

Nasopharyngeal swabs in STGGB will be cultured for the detection of respiratory bacterial pathogens, including *S pneumoniae*, *H influenzae*, *Moraxella catarrhalis*, and *Staphylococcus aureus*. Culturing and serotyping will be conducted at the PNGIMR using standard bacteriological culture, isolation, and identification methods, as previously described [27,33,34]. Briefly, 10 μL aliquots of STGGB samples will be inoculated onto horse blood agar, chocolate agar, gentamicin blood agar (5 μg/mL), and bacitracin chocolate agar (300 μg/mL) and incubated at 37 °C in 5% carbon dioxide for 18 to 24 hours. Bacterial growth will be semiquantified on the primary culture plates using a 7-point density scoring system (0-6), with scores of 1 to 3 indicating low-density colonization and 4 to 6 indicating high-density colonization.

Colony morphology and standard confirmatory tests will be used for bacterial identification. Presumptive *S pneumoniae* colonies will be confirmed by optochin sensitivity testing (≥14 mm inhibition zone) and, for optochin-resistant isolates, by bile solubility. *H influenzae* will be identified by growth characteristics on selective media and confirmed using X and V factor dependency tests. Up to 4 morphologically distinct pneumococci will be selected and serotyped using the Quellung reaction with commercially available antisera (Statens Serum Institut). *H influenzae* will be serotyped by slide agglutination (Remel). Antimicrobial susceptibility will be determined using the Kirby-Bauer disc diffusion method, with confirmation of suspected resistance by ETEST strips (bioMérieux) and interpretation according to Clinical and Laboratory Standards Institute breakpoints.

Samples will also be stored for future molecular analysis of total bacterial load and species-specific load using qPCR assays targeting bacterial DNA and pathogen-specific sequences.

#### Vaccine Antibody Responses (Serology)

Serum IgG antibody concentrations against PCV13 serotypes will be measured in blood samples collected at ages 1 and 4 months using a multiplexed immunofluorescent microsphere assay established at The Kids Research Institute Australia [35]. For each serotype, geometric mean concentrations and the proportion of children in each group with IgG levels of ≥0.35 μg/mL (considered the serological correlate of protection against invasive pneumococcal disease) will be calculated at both time points (ie, before immunization and 1 mo after the third PCV13 dose).

IgG responses to other childhood vaccines, including hepatitis B, DTwP, and Hib, will also be assessed using aliquots of the same serum samples. These will be analyzed using an in-house multiplexed immunoassay developed at The Kids Research Institute Australia laboratories [36]*.*

#### Systems Biology

Systems biology involves the application of different technologies that can detect all proteins, metabolites, gene transcripts (RNA), and cell types present in a blood sample taken at a specific time (proteomics, metabolomics, and transcriptomics). In this study, these technologies will be applied to identify specific molecular pathways and biomarkers that are modulated by the intervention and may be associated with improved immune development, such as enhanced vaccine responses, or greater protection against infectious diseases. Blood samples were collected and processed in accordance with protocols used and implemented previously by the Expanded Program on Immunization Consortium in PNG [32]. Processed blood samples will be stored at the PNGIMR until sufficient funding is secured to conduct these complex and high-cost analyses, at which point the samples will be shipped to the appropriate laboratories for analysis and data generation.

### Study Data and Management

All data collection forms were checked manually before entry into a password-protected electronic database management system (REDCap [Research Electronic Data Capture; Vanderbilt University]) housed at The Kids Research Institute Australia. Access to the deidentified database was accessible to authorized researchers and study personnel only at the PNGIMR and collaborating institutions. To ensure that any problems or queries were addressed as soon as possible, investigators in PNG and Australia attended fortnightly teleconferences.

### Data Safety Monitoring Board

A data safety monitoring board (DSMB) of independent clinicians from PNG and Australia was established. All SAEs were reported within 24 hours to an appointed Papua New Guinean safety monitor and the chair of the DSMB for review, followed by a final report detailing the outcome. Quarterly reports that included a summary of all SAEs, morbidities, and protocol violations as well as the status of enrollment and follow-up were prepared by the investigators and sent to the chair of the DSMB and distributed to other DSMB members. A teleconference with DSMB members and the study investigators was held every quarter.

### Sample Size Calculation

It was determined that a sample size of 50 participants per group would achieve 90% power to detect a difference in colonization rates of 30% in the probiotic group versus 5% in the placebo group, using a 2-tailed test of proportions with continuity correction at the 5% significance level. A final sample size of 65 participants per group was decided upon, taking into account a presumed 10% loss to follow-up and difficulties in timely biosample collection. On the basis of this sample size, it was estimated that the study would have 80% power to detect a 50% reduction in pneumococcal colonization rate in the probiotic group versus the placebo group at the 5% significance level.

### Statistical Analyses

The data will be cleaned before analysis. All data will be downloaded from REDCap and a backup copy archived before data cleaning. Missing data, outliers, and inconsistencies will be queried and verified against source documentation. Where data require changing, the database will be updated accordingly. All queries and corresponding amendments will be documented. Per-protocol and intention-to-treat analyses will be performed using available outcome data. The distribution of missing data across the treatment groups will be described, and reasons for missingness will be explored where possible to assess whether data are missing at random.

The primary objective is to determine the feasibility and safety of treatment. The number of solicited and unsolicited adverse events as well as the number of discontinued, missed, and completed doses will be summarized descriptively by treatment group. Pearson chi-square and Fisher exact tests will be used as appropriate to determine the significance of differences between groups.

The secondary objective is to measure gut colonization by probiotic strains on the last day of treatment (d 7-d 10) and at ages 1, 3, and 4 months. The prevalence of colonization at each time point will be summarized descriptively by treatment group. Colonization status, categorized as positive or negative, will be compared between treatment groups using the Pearson chi-square test, while continuous measures of colonization (ie, cycle threshold or relative fluorescence units) will be analyzed using 1-way ANOVA.

The exploratory objectives include measuring the hospitalization rates throughout the study; nasopharyngeal carriage of *S pneumoniae* and other respiratory bacteria; IgG antibody titers to PCV13, DTwP, Hib, and hepatitis B; the kinetics of probiotic gut colonization; and maternal carriage of probiotic species at the time of delivery.

Hospitalization rates will be reported descriptively per treatment group and compared using Pearson chi-square or Fisher exact tests as appropriate.

Nasopharyngeal carriage of *S pneumoniae* and other respiratory bacteria as well as gut colonization will be summarized descriptively at each corresponding time point. A Cox regression analysis will be performed, adjusting for birth weight, sex, previous antibiotic use, and breastfeeding status. Hazard ratios, along with their 95% CIs and *P* values, will be reported.

IgG antibody titers to PCV13, DTwP, Hib, and hepatitis B will be reported descriptively at baseline (before vaccination at age 1 mo) and at age 4 months (1 mo after the third dose). The differences between treatment groups will be estimated using linear regression, adjusting for birth weight, sex, breastfeeding status, and previous antibiotic use at each time point. The model will also adjust for maternal antibody titers to diphtheria, tetanus, and pertussis when comparing IgG titers to DTwP, using prevaccination infant titers as proxy measures. All IgG levels will be log transformed before analysis to meet the normality assumptions of linear regression analysis. The corresponding coefficients, along with their 95% CIs and *P* values, will be reported.

Maternal vaginal carriage of probiotic species will be reported descriptively and compared using the Pearson chi-square test.

Ad hoc analyses will include comparisons of IgG antibody levels, nasopharyngeal carriage of respiratory bacteria, SAEs, and other growth outcomes between participants colonized and those not colonized by *B longum* subspecies *infantis* or *L plantarum*. The Pearson chi-square test, the Fisher exact test, and regression modeling will be used as appropriate. The models will adjust for the variables specified earlier.

To ensure that normality assumptions are met before parametric testing, tests for normality (eg, the Shapiro-Wilk test) and a visual assessment of distribution using histograms will be carried out and the results reported. Where necessary (eg, antibody titers), the raw data will be log transformed to achieve a normal distribution.

The results of the analysis will be reported according to the CONSORT (Consolidated Standards of Reporting Trials) guidelines.

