### Study Design and Objectives

In this pilot study, we aimed to evaluate the administration of 2 different synbiotic formulations compared to placebo in newborns in PNG during the first week of life. The study design was a double-blind, randomized, placebo-controlled trial in which newborns received 1 of 2 synbiotic formulations or a placebo over 7 consecutive days, with the first dose given before the newborn was aged 72 hours and administration completed within the first 10 days of life. The overall objective is to generate data that will inform the design and implementation of a larger, definitive clinical trial in infants in PNG, including the assessment of clinical end points.

The primary pilot study objectives were (1) safety in terms of intolerance (diarrhea, vomiting, abdominal distension, and weight gain) or probiotic sepsis during the 7-day supplementation period, leading to the cessation of the study medication; and (2) the feasibility and cultural acceptability of daily probiotic administration (the proportion of children who received all 7 daily doses of supplementation without missing any). The secondary objective was to demonstrate the colonization of the gut by probiotic strains at age 1 week and at ages 1, 3, 4, and 6 months. The exploratory objectives included (1) hospitalization rates until age 6 months, (2) nasopharyngeal carriage of *Streptococcus pneumoniae* and other respiratory tract bacteria at age 2 weeks and at ages 1 and 4 months, (3) immunoglobulin G (IgG) antibody responses to childhood vaccination (PCV13; diphtheria, tetanus, and whole-cell pertussis [DTwP]; *Hemophilus influenzae* type b [Hib]; and hepatitis B), (4) the kinetics of probiotic colonization at various time points over the first 6 months of life, and (5) maternal carriage and colonization by probiotic species and pathogens at the time of delivery.

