**Figure 2 figure2:**
[figure not shown]
Flowchart of participant enrollment and visit completion. Of the 244 participants enrolled, 169 (69.3%) completed the study, with no substantial differences between treatment groups. “Family moved out of area,” “Lost to follow-up,” and “Withdrew consent” indicate study terminations, whereas “Missed visit” refers to skipped visits where participants remained enrolled.

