### Feasibility

Of the 244 enrolled infants, 218 (89.3%) successfully completed the daily intervention from day 1 to day 7. Of the 26 newborns who did not complete daily treatment, 10 (38%; *L plantarum* group: n=4, 40%; *B longum* subspecies *infantis* group: n=5, 50%; and placebo group: n=1, 10%) were early study terminations, and 16 (62%; *L plantarum* group: n=5, 31%; *B longum* subspecies *infantis* group: n=6, 38%; and placebo group: n=5, 31%) missed ≥1 doses (n=15, 94% missed a single dose, and n=1, 6% missed 2 doses) but continued in the study. Among the 10 participants who exited the study early, in the *L plantarum* group, 2 (50%) of the 4 participants received only 1 dose, 1 (25%) received 3 doses, and 1 (25%) received 6 doses; in the *B longum* subspecies *infantis* group, 1 (20%) of the 5 participants received 2 doses, 1 (20%) received 4 doses, 1 (20%) received 5 doses, and 2 (40%) received 6 doses; and in the placebo group, the participant lost to follow-up (1/1, 100%) received only 1 dose.

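### The primary safety objective is given only between-arm significance tests and no interval, so a non-significant result could not support a conclusion of safety

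*Protocol article*

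**What the plan says.** In the protocol article, Study Design and Objectives makes safety the first primary objective: "safety in terms of intolerance (diarrhea, vomiting, abdominal distension, and weight gain) or probiotic sepsis during the 7-day supplementation period", qualified as "leading to the cessation of the study medication". It gives no expected rate for this event and no rate that would be unacceptable.

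Statistical Analyses first promises description: "The number of solicited and unsolicited adverse events as well as the number of discontinued, missed, and completed doses will be summarized descriptively by treatment" arm. The inferential step follows: "Pearson chi-square and Fisher exact tests will be used as appropriate to determine the significance of differences between groups". Nothing else is planned for safety. Later in the same section, 95% CIs are specified for the hazard ratios from the exploratory Cox models and for the coefficients of the exploratory IgG regressions.

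Sample Size Calculation rests on gut colonization: 50 per group for "90% power to detect a difference in colonization rates of 30% in the probiotic group versus 5% in the placebo group", raised to 65. A second power statement concerns pneumococcal carriage. Assent and Enrollment gives the later target of 80 per arm. The Abstract's Conclusions state that supplementation is feasible and safe, while its Results say that data analysis is still under way.

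**The concern.** A test of difference can raise an alarm. When it fails to reject, it does not say how much harm remains compatible with the data; only an interval does that. The primary safety event is one that stops dosing in healthy newborns, so few events are likely, and with few events p > 0.05 is a common result even when a product causes harm.

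The pilot is meant to inform a larger trial. If the safety comparison arrives as a p-value alone, the planners of that trial learn that nothing was significant but not which excess risks have been ruled out. The Abstract's conclusion makes this more pressing, because a later non-significant table would look like confirmation of it.

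**Working it through.** **1. The plan's own sample size.** Inputs from Sample Size Calculation: 30% v 5%, two-sided 5%, 90% power, continuity correction.

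- Unpooled variance: (1.960 + 1.282)² × (0.30×0.70 + 0.05×0.95) / 0.25² = 43.3.
- With continuity correction: (43.3/4) × [1 + √(1 + 4/(43.3×0.25))]² = 51.0.
- The arcsine variant with the same correction gives 49.6.
- Exact power of the continuity-corrected test at 50 per group is 89.9%.

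The stated 50 is reproduced, so there is no sample-size error. The calculation does not concern safety.

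**2. How often the planned test misses harm.** Inputs: 80 per arm (Assent and Enrollment); one synbiotic v placebo; two-sided 5%, which is assumed because no level is stated for the safety test. Event rates are also assumed. For each pair of rates, the binomial probabilities of all outcome tables with p > 0.05 are summed.

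| Placebo v synbiotic | Missed by Fisher | Missed by Pearson (uncorrected) | Mean expected events per arm |
|---|---|---|---|
| 1% v 5% | 89% | 70% | 2.4 |
| 2% v 8% | 74% | 61% | 4.0 |
| 2% v 10% | 56% | 43% | 4.8 |
| 5% v 10% | 86% | 79% | 6.0 |
| 5% v 15% | 52% | 43% | 8.0 |
| 5% v 20% | 21% | 15% | 10.0 |

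The last column is 80 × (p1 + p2)/2. If Fisher is used when the expected count is below 5 (a common convention, assumed here), the Fisher column applies to the first three rows and the Pearson column to the rest.

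**3. Where the primary event probably lies.** Follow-Ups and Early Study Terminations reports one infant in 244 (0.4%) withdrawn by the physician for medical reasons, unrelated to the intervention. This is not the safety event rate, but it makes a low rate plausible.

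**4. What significance requires when placebo has no events.** For 0/80 v 5/80, two-sided Fisher p = 2 × C(80,5)/C(160,5) = 0.059. For 0/80 v 6/80, p = 0.028. Five infants stopping one synbiotic against none on placebo would be reported as non-significant.

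**5. What intervals would say.**

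- 0 events in 80: exact two-sided 95% upper limit 1 − 0.025^(1/80) = 4.5%; one-sided 95% limit 1 − 0.05^(1/80) = 3.7%.
- Difference between two arms of 80 with a common rate p: approximate half-width 1.96 × √(2p(1−p)/80), which is 4.3, 6.8 and 9.3 points at p = 2%, 5% and 10%.

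**The case against.** Five points can be made for the plan.

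- **No rule equates p > 0.05 with safety.** This is correct. A reader might infer such a rule from the tests and the Abstract together, but the article never states one. The Abstract's claim was made while analysis was ongoing, and the article shows no by-arm comparison of adverse events. The point is that the one inference planned cannot carry a safety conclusion, not that the authors have already misread a test.
- **Power depends on the harm considered.** This also stands. It would be tempting to say that the test misses relevant harm in most cases, but the article does not define relevant harm. Pearson detects 2% v 10% and 5% v 15% more often than not, and either test usually detects 5% v 20%. The tests also cover all solicited and unsolicited events, some of which may be common: at 20% v 40%, power is 75% (Fisher) or 80% (Pearson).
- **This is a pilot with independent monitoring.** Limited power is inherent in a pilot, and the data safety monitoring board reviewed serious events throughout. But monitoring sets no inferential criterion, and a small sample is a reason to estimate with intervals rather than to test.
- **Intervals may be in an unseen analysis plan, and readers can compute them from the counts.** Both are possible. The criticism is of the method that the article does state, beside named intervals for exploratory outcomes.
- **Exits during dosing might seem to show harm.** Feasibility lists 4 and 5 early terminations on the synbiotics and 1 on placebo, and a reader might see a signal. The article does not support that. Across the trial, all 75 terminations are attributed to loss to follow-up (37), moving away (28), withdrawn consent (9) or one unrelated medical withdrawal. These are retention data and none is documented as a primary safety event.

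**Conclusion.** The point holds. For a primary objective, the article fixes difference tests as the only inference and names no interval. By itself, a non-significant result cannot support safety at any base rate; that conclusion needs none of the assumed rates.

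The size of the problem does depend on them. At 80 per arm, two-sided 5% and one synbiotic v placebo, Fisher/Pearson miss 89%/70% at 1% v 5%, 74%/61% at 2% v 8% and 86%/79% at 5% v 10%, but only 21%/15% at 5% v 20%. Low rates are plausible for an event that stops dosing, but they are not documented.

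This is a cheap improvement. It shows neither an error in the sample size nor harm from either product.

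**What to change.** In the primary safety analysis:

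1. For each arm, report the proportion of infants with the primary safety event (intolerance or probiotic sepsis leading to cessation) with an exact (Clopper-Pearson) 95% CI.
2. For each synbiotic separately, report the risk difference v placebo with a 95% CI, for example Newcombe's.
3. Treat any chi-square or Fisher p-value as supplementary, and state that non-significance will not be taken as evidence of safety.
4. Word the safety conclusion, including the Abstract's, by what the upper bounds exclude. With 0 events in 80, for example, the statement would be that rates above about 4.5% are excluded (two-sided 95%).

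The article describes analysis as ongoing, so this can still be adopted, preferably before the by-arm safety tables are examined. It needs a few sentences of analysis text and no new data. The cost is a more cautious safety statement than the present one.

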**Methods:**

Following ethics approvals in 2018 and 2019, and receipt of the synbiotic preparations in September 2020, healthy neonates (<72 h old; n=244) were recruited between October 2020 and June 2023 and randomly assigned in a double-blind manner (1:1:1) to receive an oral preparation containing *Lactiplantibacillus plantarum*, *Bifidobacterium longum* subspecies *infantis*, or placebo for 7 consecutive days. Follow-up continued for 6 months, with rectal swabs, stool, blood, saliva, and nasopharyngeal swabs collected before the intervention; on day 7; at age 2 weeks; and at ages 1, 3, 4, and 6 months. Ongoing analyses will assess probiotic gut colonization, bacterial nasopharyngeal carriage, and antibody responses to routine childhood vaccines (*Hemophilus influenzae* type b; hepatitis B; 13-valent pneumococcal conjugate vaccine; and diphtheria, tetanus, and whole-cell pertussis) as well as hospitalization and infection rates among the intervention groups compared to the placebo group.

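### Gut colonization is to be tested by three-arm omnibus tests, although the question and the sample size are synbiotic versus placebo; no formal contrast or estimate against placebo is named

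*Protocol article*

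**What the plan says.** The trial has three arms, allocated 1:1:1. Study Design and Objectives in the Protocol article puts the question against placebo: "we aimed to evaluate the administration of 2 different synbiotic formulations compared to placebo in newborns in PNG". The abstract's Methods likewise speak of outcomes "among the intervention groups compared to the placebo group". On the secondary outcome itself: "The secondary objective was to demonstrate the colonization of the gut by probiotic strains".

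Sample Size Calculation follows that framing. It takes 50 per group for 90% power to detect 30% versus 5% colonization, probiotic versus placebo, "using a 2-tailed test of proportions with continuity correction at the 5% significance level". The number was then raised to 65 per group, and the Results report a later target of 80 per group.

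For the secondary objective, Statistical Analyses gives prevalence by arm at each time point, and then: "Colonization status, categorized as positive or negative, will be compared between treatment groups using the Pearson chi-square test". Continuous measures "will be analyzed using 1-way ANOVA". It names no contrast with placebo, effect measure, confidence interval or follow-up comparison for this outcome. A Cox model, in a paragraph covering nasopharyngeal carriage and gut colonization, will give hazard ratios with 95% CIs, but no reference arm is stated.

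**The concern.** With three arms, a 1-way ANOVA F test has the null that all three means are equal. A chi-square across the arms has the corresponding null for proportions. Neither null is that a given synbiotic equals placebo, which is the hypothesis the trial was sized to test. A significant result licenses only the statement that the arms are not all alike.

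This matters because the pilot is meant to inform a larger trial, and there are two different products. A reader will want to know, for each one, how far its colonization exceeds placebo and how precisely that is known. The secondary analysis as written gives a P value that answers neither question. By contrast, the article plans coefficients with confidence intervals for the IgG outcomes, which are only exploratory.

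**Working it through.** **Inputs.** From Sample Size Calculation: 30% versus 5%, two-sided 5% level, continuity-corrected test of two proportions, 50 and then 65 per group. From Results, Assent and Enrollment: 80 per group. From Statistical Analyses: Pearson chi-square and 1-way ANOVA between treatment groups. The patterns 30/5/5% (one product raised) and 30/30/5% (both raised) apply the article's own two rates to three arms; placebo is listed last.

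**1. Reproduce the stated power.** With x1 and x2 positives out of n per group and p̄ = (x1 + x2)/(2n), reject when (|x1 − x2| − 1)² / [2n p̄(1 − p̄)] > 3.841. Exact enumeration over the two binomials at n = 50 gives power 0.899, in agreement with the stated 90%. The design is therefore powered on a two-group comparison.

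**2. Three-arm test under the two patterns.** With total t = x1 + x2 + x3 and p̄ = t/(3n), reject when Σ(xi − t/3)² / [n p̄(1 − p̄)] > 5.991 (2 df). Exact enumeration over three binomials gives:

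| n per arm | One product raised (30/5/5%) | Both raised (30/30/5%) |
|---|---|---|
| 50 | 0.968 | 0.956 |
| 65 | 0.992 | 0.990 |
| 80 | 0.998 | 0.998 |

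The reason is visible in the spread of the rates:
- 30/5/5% has mean 13.33% and squared deviations 0.1667² + 2 × 0.0833² = 0.0278 + 0.0139 = 0.0417.
- 30/30/5% has mean 21.67% and squared deviations 2 × 0.0833² + 0.1667² = 0.0139 + 0.0278 = 0.0417.

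The spread is the same in both, and the test responds to spread, not to which arm differs from which.

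**3. What the direct comparison would show.** Under 30/5/5%, simulation (200,000 runs) has the uncorrected comparison of the unraised product with placebo rejecting about 4 to 5% of the time at 50, 65 and 80 per arm. At 65 per arm, about 95% of simulated trials give a significant omnibus test while that product does not differ significantly from placebo. The direct contrast separates the two patterns; the omnibus P value does not.

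**4. Can the trial support two contrasts?** Exact power of the continuity-corrected two-group test for 30% versus 5%. The split of alpha (0.025 each) is an assumption and is not in the article.

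| n per group | alpha 0.05 | alpha 0.025 each |
|---|---|---|
| 50 | 0.899 | 0.825 |
| 65 | 0.968 | 0.935 |
| 80 | 0.989 | 0.978 |

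As a check on attrition, Table 1 shows 168 rectal swabs at 6 months, the smallest count. That is 168/3 = 56 per arm if spread evenly (an assumption). At n = 56 the powers are 0.934 and 0.878.

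**The case against.** The strongest reply has three parts, and each stands in some measure.

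- **The assays are species-specific.** Laboratory Procedures describes a separate singleplex qPCR for each organism, and prevalence is reported by arm. On a given assay only one arm received the organism, so a reader would usually see which arm drives a difference. One might infer from the omnibus test that the trial could not show which product colonizes, or that the two species are merged into one positive/negative status. The article supports neither; what is missing is the formal comparison and its interval.
- **The chi-square wording is not explicit.** It does not say three by two, and pairwise follow-up may sit in an analysis plan that is not shown. The omnibus reading is certain for the ANOVA and only the natural one for the chi-square. Even so, the article does fix its tests for this outcome, and they are not the test that it used for sizing.
- **This is a secondary outcome of a pilot** whose primary aims are feasibility and safety. That limits the weight of the point.

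Two further inferences are tempting and should be resisted. The rejection rates of 97 to 99.8% under 30/5/5% are power against a null that is false, not a type I error rate. Nor is the omnibus test less sensitive than the planned comparison when both products work: at 30/30/5% and 50 per arm its power is 0.956, against 0.899 for the continuity-corrected two-group test.

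**Conclusion.** The point holds in a limited form. The tests named for the secondary objective do not match the question or the sample-size calculation, and that analysis provides no estimate or interval against placebo. On the article's own rates, the omnibus test at 65 per arm rejects with probability 0.992 if one product is raised and 0.990 if both are, so its P value does not distinguish the two. The Cox model does not clearly fill the gap, because its reference arm is not stated.

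The conclusion rests on reading the chi-square as a three-arm test and on 30% and 5% as the working rates. It does not rest on any shortage of power. A reader might extend it to hospitalization and adverse events, but those are exploratory or chiefly descriptive, and the point does not need them. Severity is minor to moderate.

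**What to change.** State the secondary analysis as two prespecified contrasts at each time point:

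- *L plantarum* qPCR, *L plantarum* arm versus placebo;
- *B infantis* qPCR, *B infantis* arm versus placebo.

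For colonization status, give each as a risk difference with a 95% CI and the continuity-corrected two-group test used for sizing. For the continuous measures, replace the ANOVA F test with the same two contrasts, as mean differences with 95% CIs. Say whether alpha is shared between the two. Keep the three-arm test as a descriptive addition only.

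The cost is a change of wording, a few more table rows, and two comparisons in place of one. The article reports analysis as ongoing and already gives dose completion by named arm. The change should therefore be dated and, if colonization has already been compared by arm, labelled as made afterwards.
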